# Double-blind placebo-controlled randomized clinical trial to assess the efficacy of montelukast in mild to moderate respiratory symptoms of patients with long COVID: E-SPERANZA COVID Project study protocol

**DOI:** 10.1186/s13063-021-05951-w

**Published:** 2022-01-06

**Keywords:** Montelukast, Dyspnea, Randomized controlled trial, COVID-19, SARS-CoV-2, Long COVID, Primary care, Quality of life, Health status

## Abstract

**Background:**

The coronavirus disease 2019 (COVID-19) pandemic continues to affect the globe. After 18 months of the SARS-CoV-2 emergence, clinicians have clearly defined a subgroup of patients with lasting, disabling symptoms. While big strides have been made in understanding the acute phase of SARS-CoV-2 infection, the pathophysiology of long COVID is still largely unknown, and evidence-based, effective treatments for this condition remain unavailable.

**Objectives:**

To evaluate the efficacy of 10 mg oral montelukast every 24 h versus placebo in improving quality of life associated with mild to moderate respiratory symptoms in patients with long COVID as measured with the COPD Assessment Test (CAT) questionnaire. The secondary objectives will evaluate the effect of montelukast versus placebo on improving exercise capacity, COVID-19 symptoms (asthenia, headache, mental confusion or brain fog, ageusia, and anosmia), oxygen desaturation during exertion, functional status, and mortality.

**Methods and analysis:**

Phase III, randomized, double-blind clinical trial. We will include 18- to 80-year-old patients with SARS-CoV-2 infection and mild to moderate respiratory symptoms lasting more than 4 weeks. Participants will be randomly allocated in a 1:1 ratio to the intervention (experimental treatment with 10 mg/day montelukast) or the control group (placebo group), during a 28-day treatment. Follow-up will finish 56 days after the start of treatment. The primary outcome will be health-related quality of life associated with respiratory symptoms according to the COPD Assessment Test 4 weeks after starting the treatment. The following are the secondary outcomes: (a) exercise capacity and oxygen saturation (1-min sit-to-stand test); (b) Post-COVID-19 Functional Status Scale; (c) other symptoms: asthenia, headache, mental confusion (brain fog), ageusia, and anosmia (Likert scale); (d) use of healthcare resources; (e) mortality; (f) sick leave duration in days; and (g) side effects of montelukast.

**Ethics and dissemination:**

This study has been approved by the Clinical Research Ethics Committee of the IDIAPJGol (reference number 21/091-C). The trial results will be published in open access, peer-reviewed journals and explained in webinars to increase awareness and understanding about long COVID among primary health professionals.

**Trial registration:**

ClinicalTrials.govNCT04695704. Registered on January 5, 2021. EudraCT number 2021-000605-24. Prospectively registered.

## Strengths and limitations of this study

Montelukast is an authorized medicine with extensive experience of use, good tolerance, and a known safety profile at the dose used in this trial.

Currently (August 2021), several studies are evaluating the efficacy of montelukast in the acute phase of COVID-19, and two clinical trials evaluate montelukast efficacy in reducing SARS-CoV-2 hospital admissions.

In a previous empirical treatment with montelukast in a case series of patients with long COVID, clinical improvement of symptoms was observed.

Since long COVID is an emergent condition, there are no validated scales for symptoms and quality of life.

To overcome memory bias in participants, telephone calls are added between office visits.

## Background and rationale

From June 22, 2020, to June 30, 2021, 3,547,032 cases of coronavirus disease (COVID-19) have been reported in Spain, with 7.3% patients admitted to hospital, 0.7% admitted to intensive care units, and a mortality of 1.4% [1].

In patients with mild to moderate symptoms and severe to critical coronavirus disease, full recovery might take up to 2 and 3–6 weeks from the onset of symptoms, respectively [2].

A few months into the pandemic, it was observed that in some patients, symptoms persisted for more than 4 weeks. The prolongation of the disease is now known as long COVID [3–7]. Some studies estimate that long COVID affects 10% of patients with COVID-19 [8]. The probability of developing long COVID does not seem to be related to the severity of the acute phase or to some of the risk factors associated with poor prognosis (male sex, older age, and comorbidities) [6].

Current data suggest that patients with long COVID are primarily women (78.9%), between 30 and 59 years old (86.9%), and only 8.43% have been previously admitted to the hospital for SARS-CoV-2 infection. In 65% of patients with long COVID, symptoms persist at least for 6 months from the onset of the disease [9].

Long COVID is a multi-organ disease characterized by a wide range of symptoms, including cough, headache, arthralgia, fever, abdominal pain, asthenia, brain fog, and skin manifestations. Dyspnea is one of the most frequent symptoms, as well as difficulty in performing activities of daily living, including self-care and social activities [9–11].

Although much progress has been achieved in understanding the acute phase of SARS-CoV-2 infection, the physiopathology of long COVID is less known [5, 7]. It has not been yet elucidated whether chronic symptoms are directly caused by the viral infection in multiple organs, indirectly through hyperactivation of the immune system, or due to the development of autoimmunity [7].

### Physiopathology of SARS-CoV-2 infection

SARS-CoV-2 penetrates the human cell using angiotensin-converting enzyme 2 (ACE2) as a receptor. ACE2 is mainly expressed in the lung, but also in the heart, kidney, intestine, vascular endothelium, and others [12]. The inflammatory process produced at the pulmonary and extrapulmonary levels and the overall immune response have been identified as important mechanisms in the physiopathology of COVID-19 [13].

The inflammatory process is a common response to viral infections; however, SARS-CoV-2 can overactivate the immune system leading to a cytokine storm, very likely associated with disease progression and multiple organ failure [13].

The high prevalence of antinuclear antibodies and other autoimmune markers observed in patients with COVID-19 points at the potential usefulness of specific treatments [14]. Leukotrienes, pro-inflammatory metabolites that participate in the regulation of the immune response, are possibly involved in the respiratory symptoms derived from the systemic inflammation in long COVID [15–17].

Leukotriene antagonists (LTRAs) are a group of drugs used to treat symptoms of asthma and allergic rhinitis. Their bronchodilator action and inhibition of airway inflammation improve respiratory function and airway hyperresponsiveness. By decreasing the action of leukotrienes C4, D4, and E4 when binding to CysLT1 receptors in the lungs and bronchi, LTRAs diminish bronchoconstriction and inflammation [18–20].

Recent studies have proposed the use of montelukast in the acute phase of COVID-19 due to a possible antiviral and anti-inflammatory effect [21–23]. Montelukast could prevent the entry of SARS-CoV-2 into the cell because of its affinity with the ACE2 receptor, thus shortening the course and severity of the disease [22]. Moreover, it has been hypothesized that montelukast could reduce the replication cycle of the virus [23, 24].

Clinical experience in patients admitted for COVID-19 suggests that montelukast could be associated with a reduction in clinical deterioration [25]. There are currently two registered clinical trials that evaluate the efficacy of montelukast in acute SARS-CoV-2 infection in outpatients [26, 27]. The first trial will compare the efficacy of montelukast versus placebo in reducing emergency visits and hospital admissions [26]. The second trial will evaluate the effect of montelukast and favicovir in reducing hospital admissions [27]

A pilot study was carried out using montelukast off-label in patients with COVID-19 [28]. Dyspnea, chest pain, malaise, dry cough, and nasal symptoms improved, and patients could return to work sooner.

This trial is based on prior clinical results and the hypothesis that antileukotrienes can reduce the cytokine cascade of inflammation triggered by SARS-CoV-2 infection. The E-SPERANZA COVID clinical trial aims to demonstrate the efficacy of montelukast in reducing respiratory symptoms and improving the quality of life of patients with long COVID (> 4 weeks).

## Objectives

The main objective of this study is to evaluate the efficacy of 4 weeks of treatment with 10 mg/day of oral montelukast versus placebo in improving the health-related quality of life associated with mild to moderate respiratory symptoms in patients with long COVID as measured by the CAT questionnaire [29].

One of the secondary objectives is to evaluate the effect of montelukast versus placebo on improving the following: exercise capacity, COVID-19 symptoms (such as asthenia, headache, brain fog, ageusia, and anosmia), oxygen desaturation during exertion, functional status, mortality, use of healthcare resources, days of sick leave, and medication side effects. Additionally, we will evaluate antinuclear antibodies as markers of the response to montelukast.

## Methods and analysis

### Trial design

The trial design is a phase III, randomized, double-blind, placebo-controlled clinical trial of superiority, with a two-arm parallel-group design, in which patients will be randomized to study treatment or placebo (1:1 allocation ratio).

### Study setting

The study will be carried out in thirteen primary healthcare centers in four health areas of Catalonia and Aragon, Spain. The list of study sites can be found at the Spanish Clinical Studies Registry website (https://reec.aemps.es).

### Study period

The study will be carried out from August 1, 2021, to March 1, 2023.

### Participants

Subjects are aged 18 to 80 years diagnosed with SARS-CoV-2 infection and persistent mild to moderate respiratory symptoms lasting between 4 and 12 weeks since the onset of the disease. Subjects will be included in the study if they meet all the eligibility criteria shown in Table 1.

**Table 1 Tab1:** Inclusion and exclusion criteria for the study participants

**Inclusion criteria: participants are required to meet all inclusion criteria.**	
a) Individuals ≥ 18 and ≤ 80 years old with SARS-CoV-2 infection (positive SARS-CoV-2 detection test (RT-PCR), antigenic test or equivalent < 10 days from the onset of symptoms) treated in primary care.	
b) Persistent respiratory symptoms lasting for more than 4 weeks and less than 1 year.	
c) Mild to moderate dyspnea: score from 1 to 3 at the beginning of the study according to the Modified Medical Research Council (mMRC) scale.	
d) Patient must sign an informed consent form.	
**Exclusion criteria: participants meeting one or more of the following criteria will be excluded.**	
a) Severity criteria: fever> 38 °C, O_2_ saturation < 93%.	
b) Patients with pneumonia in the acute/subacute phase due to SARS-Cov-2.	
c) Patients who have required hospital admission for SARS-Cov-2.	
d) Chronic respiratory disease: chronic obstructive pulmonary disease (COPD), asthma, bronchiectasis, pulmonary fibrosis, obstructive sleep apnea syndrome (OSAS), chronic respiratory failure from any cause, and home oxygen therapy.	
e) Use of montelukast or zafirlukast ≤ 30 days prior inclusion.	
f) Use of gemfibrozil.	
g) Hypersensitivity to montelukast, lactose intolerance, or any of the excipients of study treatment or placebo.	
h) Active malignancy and current or recent chemotherapy treatment (< 6 months).	
i) Medical history of human immunodeficiency virus (HIV) infection or any severe immunosuppression.	
j) Patients who have been in a clinical trial 30 days prior to the study.	
k) Pregnancy or planning a pregnancy.	
l) Breastfeeding mother.	
m) The principal investigator considers that the subject will not be able to perform the test procedures.	

The centers and investigators of the study were chosen from the network of collaborating centers with research experience that have agreed to participate.

### Outcomes

The primary outcome is health-related quality of life associated with respiratory symptoms according to the CAT Scale [29] 4 weeks after starting the treatment. CAT is a validated scale to quantify and monitor the impact of COPD on well-being and daily life. It consists of 8 questions (rated from 0 to 5 points) and a total score of 0–40 (0–9 mild, 10–20 moderate, 21–30 severe, and 31–40 very severe). A difference of 2 or more points in health status is considered clinically significant [30].

The following are the secondary outcomes:
Exercise capacity will be measured as the number of repetitions performed in the 1-min sit-to-stand test (1MSTS) [31], which consists of sitting down and getting up from a chair with no hand support as many times as possible for 1 min while connected to a saturation monitor. Measurements include the number of repetitions and oxygen saturation before and after performing the exercise.The Post-COVID-19 Functional Status Scale (PCFS) [32] focuses on relevant aspects of daily life during post-infection follow-up. The scale is intended to help health professionals become aware of functional limitations and to determine the degree of disability.Severity of common symptoms of patients with long COVID will be evaluated using Likert scales [33] [0 (less severe) to 10 (most severe)]: asthenia, headache, mental confusion (brain fog), ageusia, and anosmia.Use of health services, counting number of visits: virtual, primary care center, emergency room, and hospital admissions.Mortality.Sick leave days at day 28 (end-of-treatment).Side effects of the drug occurring at any time of the study period will be assessed and recorded in the data collection platform eCRF.Treatment compliance (percentage of pills taken at the end of treatment) will be estimated at the end of treatment by counting the remaining pills in the bottle or, if not possible, by directly asking the patient.

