#### Inclusion visit (day 1)

Investigators will collect the following baseline information: sociodemographic data, clinical data, use of concomitant medication, health-related quality of life associated with respiratory symptoms, functional status post-COVID-19, and scoring of asthenia, headache, mental confusion, ageusia, and anosmia.

Participants will perform the 1MSTS test to evaluate the degree of dyspnea on exertion and oxygen desaturation.

A baseline blood test will be performed, including complete blood count, electrolytes, kidney function, liver function, C-reactive protein, creatine kinase, ferritin, d-dimer, type B natriuretic peptide, antinuclear antibodies, lupus anticoagulant, and quantitative anti-SARS-CoV-2 antibodies.

Patients will receive a bottle with the medication (montelukast or placebo), and an appointment for the next visit (on day 7) will be scheduled.

The patient will be asked to return the bottle with the study medication at the end of the study.

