### Statistical analysis

Baseline characteristics of the sample will be described for each group using mean and standard deviation for quantitative variables and absolute and relative frequencies for qualitative variables. Bivariate comparison of characteristics between patients taking montelukast and patients taking placebo will be carried out to verify group comparability. The Wilcoxon test will be used for the comparison of quantitative variables and the chi-square test for the comparison of qualitative variables (or the Fisher test in case of extreme distributions in the crossed tables). In all comparisons, the statistical significance will be set at 5%.

Outcome measures will be described and compared between the montelukast and placebo groups using the same statistics. No multivariate analysis will be performed.

For the primary endpoint analysis (montelukast efficacy) and secondary endpoints, we will primarily use an intention-to-treat analysis. We will also conduct a per-protocol analysis. R-4.0.2 for Windows will be used.

Additional subgroup analysis will be performed based on symptom duration (< 6 months and ≥ 6 months).

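### The five symptom outcomes are compared only in all randomized patients, although none of the symptoms is required at entry, so power is lost and the estimate diluted for symptoms that only some patients have

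*Protocol article*

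**What the plan says.** - **Objective.** The Objectives section lists, among the effects to be improved against placebo, "COVID-19 symptoms (such as asthenia, headache, brain fog, ageusia, and anosmia), oxygen desaturation during exertion" and further outcomes.
- **Entry.** Table 1 requires "Persistent respiratory symptoms lasting for more than 4 weeks and less than 1 year" and "Mild to moderate dyspnea: score from 1 to 3 at the beginning of the study" on the mMRC scale. No inclusion or exclusion criterion mentions any of the five symptoms.
- **Scale.** The Outcomes section states: "Severity of common symptoms of patients with long COVID will be evaluated using Likert scales". It rates each symptom from "0 (less severe) to 10 (most severe)]: asthenia, headache, mental confusion (brain fog), ageusia, and anosmia".
- **Baseline.** The inclusion visit on day 1 records "scoring of asthenia, headache, mental confusion, ageusia, and anosmia".
- **Analysis.** The Statistical analysis section names the Wilcoxon test for quantitative variables and then states: "Outcome measures will be described and compared between the montelukast and placebo groups using the same statistics". It rules out multivariate analysis and makes intention-to-treat the main approach for primary and secondary endpoints alike. Its only subgroup is symptom duration, below against at or above 6 months.

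**The concern.** The objective is to improve symptoms, but the comparison includes patients who do not have them. Someone with dyspnea and a normal sense of smell is eligible, scores 0 for anosmia on day 1 and has no room to improve. Such patients add tied values in both arms and no information on benefit. Their share also varies by chance between arms, which adds noise when post-treatment scores are compared.

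For a symptom that a minority has, a real benefit in affected patients may well be missed, and the reported difference would understate what those patients gained. A null result could then be taken to mean that the drug does not help that symptom. The day-1 score that would avoid this is collected, but the article gives it no stated role in an efficacy comparison.

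**Working it through.** **1. Evaluable number per arm.** The plan gives no sample size for the symptom scales, so the number comes from the primary outcome. Inputs from the Sample size section: SD 5.69, difference 2, two-sided alpha 0.05, power 0.80, 10% loss.

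n = 2 × (1.960 + 0.842)² × 5.69² / 2² ≈ 127.1, so 128 per arm.

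For losses, 128 / 0.9 = 142.2 (143 rounded up), and 142 × 0.9 = 127.8. The stated 142 per arm is reproduced to within one patient, leaving about 128 evaluable per arm.

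**2. Dilution.** Let p be the share of patients with the symptom on day 1 and d the extra fall in those patients on montelukast. The expected difference in all patients is p × d. With d = 1.5:

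- p = 15%: 0.15 × 1.5 = 0.225 points, with 128 × 0.15 ≈ 19 affected patients per arm
- p = 40%: 0.40 × 1.5 = 0.60 points, with 128 × 0.40 ≈ 51 per arm
- p = 80%: 0.80 × 1.5 = 1.20 points, with 128 × 0.80 ≈ 102 per arm

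**3. Power of the Wilcoxon test, by simulation.** Assumptions, none of them in the documents: affected patients have a day-1 mean of 6 (SD 2), fall by 1 point on placebo and 2.5 on montelukast, with residual SD 2. Scores are integers from 0 to 10, and unaffected patients stay at 0. The article does not say whether the post-treatment score or the change from day 1 is compared, so both are shown.

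| Prevalence | Post-treatment score, all patients | Post-treatment score, day-1 score ≥1 | Change, all patients | Change, day-1 score ≥1 |
|---|---|---|---|---|
| 15% | 8% | 33% | 29% | 55% |
| 40% | 19% | 74% | 73% | 94% |
| 80% | 79% | 95% | 99% | 100% |

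Repeat runs agree to within about 3 percentage points.

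**4. Sensitivity to the assumptions.** A second model gives affected patients who would not benefit a mean of 5 (SD 2.5) and compares post-treatment scores, again with 128 per arm. It shows power in all patients against power in affected patients only:

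| Effect in affected patients | 80% prevalence | 50% | 30% |
|---|---|---|---|
| 0.88 points (0.35 SD, as for the primary: 2 / 5.69) | 44% v 67% | 13% v 47% | 6% v 32% |
| 1.5 points | 88% v 99% | 35% v 90% | 13% v 70% |
| 2.0 points | 99% v 100% | 54% v 99% | 19% v 90% |

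**5. Type I error.** With no drug effect, both the all-patient and the restricted test reject in about 5% of runs at every prevalence.

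**The case against.** **The article does not say that raw post-treatment scores are compared.** This is correct. The objective speaks of improvement, day-1 scores exist, and a Wilcoxon test on change would be compatible with the ban on multivariate analysis. Much of the loss disappears if change is used: at 40% prevalence, all-patient power rises from 19% to 73%. A reader might infer that the plan ignores baseline altogether, but the text does not settle that. What stands is that restriction by the day-1 score adds power on either reading (73% to 94% on change at 40%).

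**This belongs in the analysis plan.** That would hold if the article were silent. It instead states which comparison is made, in which population, without multivariate analysis, and with one subgroup that is not presence of the symptom.

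**The intention-to-treat contrast is valid.** It is: it is unbiased for the enrolled population. But it answers a different question from whether the drug improves a symptom in people who have it.

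**The symptoms may be frequent.** The Outcomes section calls them common in long COVID. For a symptom that nearly all patients have, such as perhaps asthenia, little is lost. The documents give no prevalence in this population.

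**Restriction does not rescue a rare symptom.** This is also true. At 15% prevalence the restricted test reaches only 33% (post-treatment score) or 55% (change). In addition, 0 is labelled as less severe rather than absent, so a cut-off of 1 is a working definition that must be stated.

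**Conclusion.** The point holds as a loss of power and a diluted estimate for those of the five symptoms that only some patients have. Under the main assumptions, power in all patients against those scoring 1 or more on day 1 runs from 8% against 33% (15% prevalence) to 79% against 95% (80%) on the post-treatment score, and from 29% against 55% to 99% against 100% on change. The direction does not depend on the assumed effect or prevalence; the size does, and neither is given in the documents.

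Three stronger readings are tempting and not supported:

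- That any effect is buried. The loss is small for very common symptoms, and much smaller if change is analysed.
- That a chance imbalance in who has the symptom would pass for a drug effect more often than the nominal level allows. The false-positive rate stays near 5%.
- That exertional desaturation needs the same restriction. Saturation is not a 0 to 10 score with many patients at 0, so these calculations do not carry over, and the documents offer no cut-off.

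The primary CAT outcome and its sample size are untouched.

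**What to change.** In the Statistical analysis section, pre-specify for each of the five symptoms:

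1. A comparison of change from the day-1 score, or a baseline-adjusted comparison, among all randomized patients with a day-1 score of 1 or more for that symptom. The adjusted form needs an exception to the sentence that excludes multivariate analysis.
2. The all-patient comparison, kept as supportive.
3. The number of patients per arm with the symptom on day 1, and new occurrence among those scoring 0.

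State that the day-1 score is taken before the first capsule. Table 2 places it in the first column after allocation, but with blinding and no dose yet taken, treatment cannot have influenced it and the subset remains a randomized comparison.

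The cost is wording only: no new data, visits or patients. The downside is a smaller sample per symptom and a result that applies to patients with the symptom rather than to everyone enrolled.

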### Sample size

In the data published by Wang et al. [34] to evaluate an intervention in stable COPD patients, a weighted common standard deviation of the CAT score of 5.69 was observed. Basing the sample calculation on these data, in a study of the superiority of montelukast compared to placebo with an intention-to-treat analysis, accepting an alpha risk of 0.05 and a beta risk under 0.2 in a two-tailed contrast, 142 individuals in the treatment group and 142 in the control group are needed to detect a difference of 2 units. We assume a 10% loss to follow-up rate.

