### Intervention

The intervention consists of a 28-day treatment, with oral administration of 1 capsule per day (research drug or placebo). Participants belonging to the:
Intervention group will be treated with montelukast 10 mgControl group will receive the placebo (microcrystalline cellulose)

The Pharmacy Department of Bellvitge University Hospital will encapsulate montelukast and the placebo.

Follow-up consists of a series of office visits (days 1, 14, and 28) and telephone visits (days 7, 21 and 56), as described in Fig. 1 and Table 2. A window period of ± 2 days for each visit will be accepted.

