#### Phone call (days 7, 21, and 56)

Health-related quality of life associated with respiratory symptoms, post-COVID-19 functional impairment, and symptom progression will be evaluated by means of a telephone call using the same questionnaires. Information regarding the number of visits to the health center, primary and/or hospital emergency care, and hospitalization since the previous visit will be assessed, as well as the use of concomitant medication, evaluation of adverse events, and compliance with study medication.

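### Health-service use is compared as a raw visit count with no allowance for time observed, which would bias the comparison if loss to follow-up differs between arms and partial counts are kept

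*Protocol article*

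**What the plan says.** The Outcomes section of the protocol article lists, among the secondary outcomes, "Use of health services, counting number of visits: virtual, primary care center, emergency room, and hospital admissions". It gives no time window and no denominator. In the same list, days of sick leave are tied to a time point, day 28.

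On collection, the section on the phone calls says "Information regarding the number of visits to the health center, primary and/or hospital emergency care, and hospitalization since the previous visit will be assessed". Table 2 schedules health-service use at every contact after day 1, that is days 7, 14, 21, 28 and 56.

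On analysis, the Statistical analysis section says "The Wilcoxon test will be used for the comparison of quantitative variables". It carries this over to outcomes: "Outcome measures will be described and compared between the montelukast and placebo groups using the same statistics". It adds "No multivariate analysis will be performed". The analysis is primarily by intention to treat, with a per-protocol analysis as well.

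On attrition, the Sample size section says "We assume a 10% loss to follow-up rate", as one figure with no split by arm.

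**The concern.** A visit count depends on how long someone is watched. Because each contact asks about the period since the one before, the count stops at the last contact attended. A patient lost after day 14 can have at most 14 of the 56 days of visits recorded. A rank test on the counts would place that patient among the low users, next to patients observed for the whole period.

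Use of healthcare resources is a named secondary objective. If more patients left the montelukast arm, part of an apparent saving in care would be missing observation. If more left the placebo arm, a real saving would be understated.

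**Working it through.** **The plan's own figure.** The article gives no figure for health-service use, so the only one to reproduce is the sample size. With SD 5.69, difference 2, two-sided alpha 0.05 and power 0.80:

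n per arm = 2 × (5.69 × (1.960 + 0.842) / 2)² = 127.06; 127.06 / 0.90 = 141.2, rounded up to 142.

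The stated 142 per arm therefore reproduces and already includes the 10% loss. It is used below as the number randomised per arm.

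**Expected bias with no drug effect.** Let d be the proportion lost in an arm and f the fraction of the 56 days observed before loss. If partial counts are kept and visits occur at a constant rate, the ratio of mean counts, arm B to arm A, is

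[1 − d_B(1 − f)] / [1 − d_A(1 − f)].

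Arm-specific loss and f are assumptions, since the article gives neither. If loss is spread evenly over days 7 to 28, its mean is day 17.5, so f = 17.5/56 = 0.3125 and 1 − f = 0.6875.

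- 10% v 10%: 1.00.
- 7% v 13%: (1 − 0.13 × 0.6875) / (1 − 0.07 × 0.6875) = 0.911/0.952 = 0.957, about 4% fewer visits.
- 5% v 15%: (1 − 0.15 × 0.6875) / (1 − 0.05 × 0.6875) = 0.897/0.966 = 0.929, about 7% fewer visits.
- 5% v 15% with f from 0.25 to 0.75: 0.922 to 0.975, about 3-8% fewer visits.

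**False-positive rate of the Wilcoxon test.** Simulated with 142 per arm, no drug effect, overdispersed counts (gamma-Poisson, shape 1), partial counts kept and trial contacts not counted:

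| Setting | Equal 10% | 7% v 13% | 5% v 15% |
|---|---|---|---|
| Mean 0.5, 1 or 2 visits per 56 days; loss evenly over days 7-28; 1,500 trials | 4.1-5.9% | 6.1, 5.0, 7.5% | 7.4, 7.1, 9.3% |
| Mean 1 or 3 visits per 56 days; last contact day 0, 7, 14, 21 or 28, equally likely; 2,000 trials | 5.1, 6.5% | not run | 8.8, 10.3% |

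The Monte Carlo standard error near 5% is √(0.05 × 0.95 / 1,500) = 0.6 percentage points, so the 7% v 13% results are barely distinguishable from nominal.

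**With the rate model alongside.** In a further simulation the Wilcoxon test rejected in about 5% of trials at equal loss, 4-8% at 7% v 13% and 6-10% at 5% v 15%. A quasi-Poisson model with a log-time offset stayed at 3-6%.

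**The case against.** The strongest reply is that the bias needs two things the article does not state: unequal loss, and incomplete counts used as if complete. The article gives a single 10% figure and describes montelukast as well tolerated. Follow-up is short and has the same planned length for everyone. The article does not say whether an early leaver's count is kept, set to missing or imputed. It does not even say that visits are summed to day 56 rather than compared interval by interval. Such rules are commonly left to the full protocol or the SAP. All of this stands, and it makes the point conditional. What it does not remove is that the comparison the article does fix, a rank test on counts, has no place for time observed. Intention to treat also points towards keeping early leavers, though it does not settle how their counts are treated.

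Two stronger readings are tempting and should not be drawn:

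- **That the plan, as written, makes the arm with more drop-outs appear to use less care.** That follows only under both conditions above. With equal loss the ratio is 1.00 and the error rate is nominal.
- **That the trial's own contacts are counted.** The counted categories include virtual and primary care visits, and the trial itself runs in thirteen primary healthcare centers with office and telephone contacts. The overlap is real, but the article does not say these contacts count. Asking at each trial contact about care since the previous one suggests that the care in between is what is meant. Much larger error rates would follow if scheduled contacts were counted, but they would rest on silence and an unnatural reading, so none is claimed here.

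**Conclusion.** The point holds in conditional form. The stated method compares raw visit counts and ignores observation time although loss is planned for. Given unequal loss and retained partial counts, the arm with more loss is biased towards fewer visits. At an assumed 5% v 15% the bias is about 7% fewer, with a false-positive rate of roughly 6-10%. At 7% v 13% the effect is slight, and at equal loss there is none. These sizes also rest on assumed visit rates, overdispersion and timing of loss. The primary CAT comparison and the sample size are unaffected, so this is a desirable improvement and not a serious flaw.

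**What to change.** Define the outcome as visits from day 1 to day 56. Compare arms by a rate ratio with 95% CI from a quasi-Poisson or negative binomial model, with arm as the only term and log(days observed, up to day 56) as offset. Keep early leavers in the analysis with their shorter time. A patient with no contact after day 1 has no observed time and cannot enter the model, so report the number of such patients by arm. The model has no covariates and so fits the intent of the article's exclusion of multivariate analysis, but the text should say so to avoid dispute.

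As a clarification only, add that contacts scheduled by the protocol are not counted as health-service use.

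The cost is a few sentences and no new visits. The time observed needs each patient's last contact date, which a scheduled-visit data form should supply, although the article does not say so. The downside is small: the model assumes that visits after drop-out would have continued at the rate seen before it, which fails if patients leave because their health or care use is changing.
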